### Secondary outcome

The secondary outcomes will be to evaluate the fruit and vegetable intake of women and children, post-harvest practices among farmers, traders, and women, food waste behaviour of women, BMI-for-age in women and children, the knowledge level of women regarding fruits and vegetables, and the impact of these on nutritional outcomes (Table 2).

**Table 2 tab2:** Table of primary and secondary outcomes.

Outcome type	Outcome	Measurement method	Assessment time points
Primary	Anaemia status in women and children	Haemoglobin testing (Hemocue 501 meter)	Baseline and post-intervention
Primary	Dietary Diversity Score (DDS)	24-h dietary recall and food group classification	Baseline and post-intervention
Secondary	Household food waste behaviour	Structured food waste behaviour questionnaire	Baseline and post-intervention
Secondary	Fruit and vegetable intake	Food Frequency Questionnaire (FFQ)	Baseline and post-intervention
Primary	Post-harvest handling knowledge/practices	Survey and Focus Group Discussion	Baseline
Primary	Anthropometric measurements (BMI, z-scores)	Height, weight using WHO protocol	Baseline and post-intervention

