## Study objectives

The primary objective of this study is to investigate the relationship between post-harvest losses of fruits and vegetables and the nutritional status of women and children in the Ho West District of Ghana. Specifically, the study aims to estimate the extent and drivers of post-harvest losses at the farm, retail, and household levels, to determine the nutrient losses associated with post-harvest waste of fruits and vegetables, to examine the relationship between the nutritional status of women and children in households and fruits and vegetables losses and to evaluate the effect of a structured community-based nutrition education and counselling intervention on post-harvest practices, fruit and vegetable consumption, and nutritional outcomes.

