### Study design

The study is an experimental trial with an untreated control group, adhering to the Consolidated Standards of Reporting Trials (CONSORT). The study will be conducted in three main phases: Phase I (problem identification and quantification), Phase II (intervention development and implementation) and Phase III (evaluation of intervention). The outcome of the study will be assessed twice, at baseline and post-intervention. The intervention will be tested on households, which will receive structured education on fruit and vegetable intake, as well as methods for waste and food preservation. Women in the household will be educated on food preservation methods and how to store various types of fruits and vegetables at home. They will receive intervention for 6 months.

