### Sample size calculation

Sample size was calculated using STATA software, accounting for a 30% (25) anticipated improvement in nutrition and reduction in waste due to the intervention. A total of 140 households (70 per group) were determined to be sufficient, assuming 80% power, a 5% significance level, and 10% non-response.

Separate sample size calculations were done for farmers and market vendors using a single proportion in STATA 14. The total sample size for these groups was set at 70, incorporating a 10% non-response rate. The estimated proportion of postharvest loss was 20%, confidence level was 0.95%, level of significance was 0.05.

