#### Baseline assessment

Data will be collected using semi-structured questionnaires, a widely applied method for exploring household-level food storage and nutritional behaviours in community-based research (26, 27). The availability of fruits and vegetables, as well as their storage conditions, will be systematically observed during household visits. A structured questionnaire will be administered to gather information on sociodemographic characteristics, the quantity of fruits and vegetables purchased, consumed, stored, and the extent of food losses encountered, approaches consistent with established value-chain assessment protocols (28). Based on the quantities of reported losses, the loss estimates will be calculated using the Food Loss and Waste Value Calculator developed by Quantis as part of the WBCSD’s FReSH program (29).

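### Table 2 schedules a listed primary outcome, post-harvest handling knowledge and practices, at baseline only, which conflicts with the effect objective, the two-assessment design and the outcome text

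*Protocol article*

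**What the plan says.** In the protocol article, Table 2 (under Secondary outcome) has six rows, four of them typed primary. One of those four is "Post-harvest handling knowledge/practices", whose method and time-point cells read "Survey and Focus Group Discussion Baseline". The other five rows, both secondary ones included, are scheduled at baseline and post-intervention.

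Three other places bear on that row:

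- Study objectives sets out "to evaluate the effect of a structured community-based nutrition education and counselling intervention on post-harvest practices", along with consumption and nutritional outcomes.
- Study design states: "The outcome of the study will be assessed twice, at baseline and post-intervention".
- The paragraph above Table 2 lists "post-harvest practices among farmers, traders, and women", and women's knowledge about fruits and vegetables, among the secondary outcomes. The Primary outcome section speaks only of nutritional status.

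**The concern.** Knowledge and practical skill in storing and preserving produce are what the six-month programme directly teaches: in Table 1, months 3 and 4 are given to preservation and storage. An effect on this outcome needs a value after the programme, in both arms, and the schedule provides none.

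Two things are at stake. First, one part of a stated objective would reach the analysis without the data listed for it. Second, knowledge is an early link between the education and any change in haemoglobin, diet or growth. If those outcomes do not move, the trial could not say whether women failed to learn the material or learned it without nutritional benefit.

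The label adds a separate problem. The same construct is primary in the table and secondary in the text, so its place in the outcome hierarchy and in the multiplicity plan is not fixed.

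**Working it through.** No arithmetic applies, because the point concerns the schedule and label of one outcome. The check sets the passages side by side.

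1. **Time points in Table 2.** Anaemia status, dietary diversity, anthropometry, food waste behaviour and fruit and vegetable intake: baseline and post-intervention. Handling knowledge and practices: baseline. That is five rows against one.

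2. **What an effect estimate needs.** Write Y0 for the baseline value and Y1 for the post-intervention value. A post-intervention contrast is mean Y1 (intervention) minus mean Y1 (control). A contrast of changes is mean (Y1 − Y0) in the intervention arm minus the same quantity in the control arm. Both need Y1. With Y0 alone, only a baseline difference between arms exists, and it precedes the programme. The t-tests in Statistical analysis, within and between groups at both times, cannot be carried out in full for this row.

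3. **Whether the outcome is measured at endline elsewhere.**
   - Food waste behaviour questionnaire (scheduled twice, secondary): its five listed variables are self-reported waste, intention to reduce waste, attitudes, storage and planning habits, and food preparation routines. Part of women's household practice is therefore compared between arms. None of the five is knowledge, and Table 2 lists the questionnaire as a different outcome.
   - Home-visit checks of storage (Adherence strategies and monitoring procedures): these monitor compliance with the programme and are not described as an outcome assessment in both arms.
   - Month 6 review (Table 1): it is part of the intervention, so it gives no control-arm value.

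4. **Women's knowledge.** It is named as an outcome in the paragraph above Table 2. The only row that covers it is the baseline-only one, so it has no scheduled endline.

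5. **Loss quantities.** Amounts purchased, consumed, stored and lost are described under Baseline assessment, where "Based on the quantities of reported losses, the loss estimates will be calculated". The sample size rests on an "anticipated improvement in nutrition and reduction in waste due to the intervention". Limitations of the study says that the design tracks changes in household waste over time. The article neither states nor rules out repetition of the quantity questions at endline.

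6. **Label.** Table 2 says primary; the paragraph above it says secondary. Both cannot stand.

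**The case against.** The strongest reply is that the table cell or its label is a slip. Study design says in general terms that outcomes are assessed twice, which would make the time point the error. Alternatively, the row belongs to Phase I, problem identification and quantification: it uses a survey and focus groups, the outcome text extends practices to farmers and traders, and no intervention is described for those two groups. Baseline-only measurement would then be right and the word primary would be wrong. Either reading is plausible. Neither removes the conflict, because a general sentence does not settle a specific schedule, and the Phase I reading leaves the objective on practices without this outcome's data.

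Three stronger readings are tempting, and the document does not support them:

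- *The trial cannot estimate any effect on practices.* A reader might infer this from the table row, but storage and planning habits, preparation routines and self-reported waste are measured twice in the food waste behaviour questionnaire.
- *Household loss is not measured at endline.* A reader might infer this from the heading Baseline assessment. Limitations of the study says that household waste is tracked over time, and the schedule figure is not available here. Repetition of the quantity questions is unstated, which is a weaker point.
- *Half of the planned effect has no endline.* Sample size calculation names improved nutrition and reduced waste together. It does not divide the 30% between them or say that waste means quantity lost.

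It is also fair to say that a condensed article leaves instrument detail to the full protocol. The finding does not rest on omitted detail: Table 2 states a time point and a label that other sections contradict.

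**Conclusion.** The conflict is real and should be reconciled before analysis. As scheduled, one of six outcome rows, and one of the four typed primary, can give no intervention effect, and women's knowledge has no scheduled endline. What remains estimable on practices is the part covered by the secondary food waste behaviour questionnaire. The other three rows typed primary are unaffected by this point.

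The conclusion assumes that Table 2 is followed as written. If the survey was in fact repeated in both arms, the defect reduces to a wrong cell and an inconsistent label. If the row was always meant as Phase I description, it reduces to a wrong label and an objective that claims more than the schedule supports.

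**What to change.** - For women in both arms, change the Table 2 time point to baseline and post-intervention, and repeat the same survey items at the planned endline visit. The focus groups need not be repeated.
- Make the farmer and trader part a descriptive baseline measure, separate from the trial outcomes.
- Give the construct one label, primary or secondary, in both Table 2 and the paragraph above it.
- State whether the questions on quantities purchased, stored and lost are repeated at endline.
- If endline visits are already complete, reclassify the row as baseline descriptive and limit the effect claim in Study objectives to the practices that the food waste behaviour questionnaire covers.

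Version 1.0 is dated 9 June 2025 and data collection was planned to run to 31 July 2025, so which branch applies depends on how far endline had progressed.

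The cost is an amendment to one table row and the matching text, reported as the Protocol amendments section requires. If endline is still open, add some interview time for about 140 women (70 per group) at a visit already planned; the article gives no basis for putting minutes on it. The fallback needs no new data but gives up the effect on handling knowledge and practices as listed.

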### Intervention design and strategy

This study will implement a structured, community-based nutrition education and counselling program targeting women and children in the intervention communities of Kpedze and Amedzofe. In contrast, Abutia Kissiflui and Dededo will serve as control communities, with no intervention exposure. Such community-level strategies have been shown to improve food handling practices and reduce household-level losses in African settings (15). The aim is to enhance knowledge and practical skills on fruit and vegetable storage, reduce household-level post-harvest losses, and improve dietary practices.

The intervention will span a six-month period and will be coordinated by a trained dietitian, supported by three community health nurses. Educational meetings will occur monthly, and additional counselling will be provided through bi-weekly home visits and telephone interactions. Educational materials such as visual posters, handouts, and illustrative charts will be developed in local languages to ensure cultural relevance and ease of understanding. Group sessions will be interactive, allowing participants to ask questions and share experiences. Each session will last approximately 45 min and accommodate 5–10 women per group (Table 1).

**Table 1 tab1:** Lesson plan for nutrition education.

Month	Topic	Content	Rationale and literature support
Month 1	Importance of Fruits & Vegetables on Nutritional Status	Benefits, local examples, myths and facts	Dietary diversity and intake of micronutrient-rich foods like fruits and vegetables are critical for preventing undernutrition and anaemia in women and children (14). Awareness helps reshape food choices.
Month 2	Fruits and Vegetables Waste and Its Implications	Drivers, causes, prevention	Community-level losses reduce availability of key nutrients. Kitinoja and Kader (6) and Sheahan and Barrett (19) show that household knowledge on proper handling can reduce loss and improve food security.
Month 3–4	Fruit and Vegetable Preservation and Storage	Low-cost storage methods (e.g., clay pot coolers, FIFO), meal planning	Ambuko et al. (3) and Stathers and Mvumi (36) support the use of low-cost post-harvest technologies in rural African communities. FIFO principles help manage perishables better.

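### Table 2 schedules post-harvest knowledge and practices at baseline only, so an effect on women's knowledge cannot be estimated and an effect on their practices only through a partial proxy

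*Protocol article*

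**What the plan says.** The last of the aims under Study objectives is "to evaluate the effect of a structured community-based nutrition education and counselling intervention on post-harvest practices, fruit and vegetable consumption, and nutritional outcomes". Study design states: "The outcome of the study will be assessed twice, at baseline and post-intervention". Intervention design and strategy describes the purpose of the package: "The aim is to enhance knowledge and practical skills on fruit and vegetable storage".

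The text under Secondary outcome names "post-harvest practices among farmers, traders, and women, food waste behaviour of women" and, later in the same sentence, "the knowledge level of women regarding fruits and vegetables". Table 2, in the same section, has one row for this material: "Post-harvest handling knowledge/practices", measured by "Survey and Focus Group Discussion". That row is typed as primary and its only time point is baseline. The other five rows (anaemia status, dietary diversity, food waste behaviour, fruit and vegetable intake, anthropometry) are all assessed at baseline and post-intervention.

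Statistical analysis plans t-tests of the outcomes of interest, within and between groups, at baseline and post-intervention.

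**The concern.** An outcome measured only before the intervention carries no information about its effect. Here that outcome is the nearest result of the teaching. The package works by education, and what women know and how they handle produce is the first step towards less waste, better diet and better nutritional status. If haemoglobin or dietary diversity does not move, the investigators will want to know whether the teaching failed to take hold or took hold without nutritional benefit. Without a two-arm endline measure of knowledge, that question can be addressed only in part, through reported behaviour.

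This is not a detail left to an unseen analysis plan. The article itself fixes the time point, and does so against its own objective.

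**Working it through.** No sample size, power or alpha figure is involved. The check compares the schedule with what the objective and the analysis need.

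**1. What the planned comparison needs.** Write Y0 for a woman's baseline value and Y1 for her post-intervention value.
- Within-group change: mean(Y1 − Y0) in each arm.
- Between-group effect: mean(Y1, intervention) − mean(Y1, control), or the difference between arms in mean(Y1 − Y0).

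Each expression contains Y1. With Y0 alone, the only available contrast is the baseline difference between arms, which speaks to comparability and not to effect. The planned multiple imputation cannot help, because a value collected from nobody in either arm gives no observed data to impute from.

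**2. Count in Table 2.** Six outcome rows; five have Y1 and one does not (6 − 5 = 1). For that row, 0 of the 140 planned households have a scheduled Y1.

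**3. Whether Y1 is collected elsewhere.**

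| Source | Knowledge | Practices | Post-intervention, both arms |
|---|---|---|---|
| Table 2, knowledge/practices row | yes | yes | no, baseline only |
| Food waste behaviour questionnaire | no | partly: storage and planning habits, food preparation routines, self-reported waste | yes, by its own Table 2 row |
| Home-visit checks of storage practices (Adherence strategies and monitoring procedures) | no | storage only | adherence monitoring; control-arm collection not stated |
| Month 6 review (Table 1) | uptake reviewed in session | uptake reviewed in session | teaching session in the intervention communities only |

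Knowledge has no two-arm post-intervention source. Practices have one partial source. It is partial by the protocol's own account: the outcome text lists food waste behaviour, post-harvest practices and women's knowledge as separate items, and Table 2 gives food waste behaviour its own row.

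**4. Conflicts within the article.**
- The baseline-only row conflicts with the objective on practices, with the two-assessment statement in Study design, and with the comparison in Statistical analysis.
- The row is typed as primary, while the text directly above the table places practices and women's knowledge among the secondary outcomes.

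**The case against.** The strongest reply is that the gap is smaller than it looks. The food waste behaviour questionnaire is given at both time points and covers much of what months 3 to 5 of the lesson plan teach: storage, meal planning and use of leftovers. It is self-reported, but so is a survey of practices. Fruit and vegetable intake and dietary diversity are also measured twice. This stands. A reader might infer that the objective on practices cannot be answered at all, or that the trial could not say whether women changed anything. The documents do not support either reading, because several behaviours are followed to endline. Nor does the objective itself name knowledge, which comes from the intervention's aim and the outcome list.

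A second reply is that the row describes the value-chain work of Phase I. Its method, a survey with focus groups, fits discussions held with farmers, traders and women, and Limitations of the study says change is tracked only at household level. On that reading, baseline only is right for farmers and traders. It does not settle the matter for women, who are the household participants receiving the education and whose knowledge and practices have no other row.

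A third reply is that Study design already promises two assessments, and that the SPIRIT schedule in Figure 1, not visible in the text reviewed, may show them. That makes this a contradiction to be reconciled and not proof that the repeat was deliberately left out. It does not remove the contradiction, since the outcome table carries the restrictive version.

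**Conclusion.** The point holds in a limited form. Table 2 fixes the knowledge and practices outcome at baseline only, against the article's objective, design statement and analysis section. If Table 2 is followed:

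- an effect on women's knowledge is not estimable;
- an effect on women's practices is estimable only for the constructs in the food waste behaviour questionnaire;
- the other five rows of Table 2 are unaffected.

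This rests on two assumptions: that Table 2 governs field work, and that Figure 1 does not schedule a repeat survey. If the repeat is in fact planned, the remaining fault is a wrong table entry. The inconsistent primary or secondary label stands in either case. The matter should be corrected, but it does not threaten the trial's nutritional outcomes.

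**What to change.** 1. In Table 2, split the row. For women, set the time points to baseline and post-intervention. For farmers and traders, who receive no intervention, keep baseline only.
2. Use the same women's survey in both arms at the planned endline visit. Compare it between arms like the other household outcomes, allowing for the allocation of whole communities, two per arm.
3. Give the row one status, primary or secondary, and make the outcome text and Table 2 agree.

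The cost is one existing questionnaire module repeated at a visit already planned, a few more interview minutes per woman, and one table edit.

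Timing matters: version 1.0 is dated 9 June 2025 and data collection was planned to run to 31 July 2025, so endline may already be complete. In that case the objective should not be deleted, because the questionnaire data answer part of it. Label the knowledge and practices row as baseline-descriptive, report openly that knowledge was not measured after the intervention, and limit any effect claim on practices to storage and planning habits, food preparation routines and self-reported waste. This costs only text, recorded as a protocol amendment.

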### Statistical analysis

Statistical package for social sciences (SPSS) (IBM Corp. Released 2022. IBM SPSS Statistics for Windows, Version 30.0. Armonk, NY: IBM Corp) will be used for the data analysis. The Kolmogorov-Smirnov and Shapiro-Wilk tests will be used to assess the normality of the quantitative data. A *p*-value less than 0.05 indicates that the data is not normally distributed, and vice versa. The characteristics of the study participants will be analysed using descriptive statistics. A chi-square test will be done to assess the relationship between categorical variables. Fisher’s exact test will be employed to determine the significance level. Parametric tests will be used to analyse normally distributed data, and non-parametric tests will be used to analyse data that is not normally distributed. Parametric tests will be presented in terms of mean and standard deviation, and non-parametric tests will be presented in terms of median (maximum-minimum). A t-test will be conducted to compare the mean differences of the outcomes of interest within and between study groups at baseline and post-intervention. Regression analysis will be conducted to predict the drivers of fruit and vegetable loss, adjusting for age and gender. Partial correlation will be used to assess the strength of association among the variables. All *p*-values will be significant at *p* < 0.05.

The primary analysis will follow the intention-to-treat (ITT) principle, including all participants as initially allocated, regardless of their adherence to the intervention protocol. This approach ensures an unbiased estimate of the intervention effect. For secondary per-protocol analyses, only participants who fully adhered to the intervention will be considered. To address missing data, particularly in outcome measures such as dietary assessments and anthropometry, multiple imputation methods will be employed under the assumption that data are missing at random. Sensitivity analyses will be conducted to assess the robustness of results. This strategy helps maintain the validity and reliability of findings despite potential data gaps.

To account for multiplicity in the analysis of primary and secondary outcomes, the study will employ a structured analytical approach. Primary and secondary outcomes will be pre-specified to avoid *post hoc* comparisons. Where outcomes are assessed at multiple time points (e.g., baseline and post-intervention), repeated-measures analysis or appropriate statistical corrections such as the Bonferroni adjustment will be applied to control the risk of Type I error. Subgroup analyses (e.g., by community or demographic characteristics) will be exploratory and clearly labelled as such to prevent overinterpretation. These steps ensure robust and reliable interpretation of findings while maintaining the statistical integrity of the study. This protocol was developed in consultation with a statistician. The statistician reviewed sample size estimations and the statistical analysis plan to ensure methodological soundness. This is reflected in the detailed statistical analysis section, which outlines methods for dealing with missing data, baseline comparability, and outcome estimation.

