## Research design and methods

### Study setting

The study will be conducted in the Ho West District of the Volta Region in Ghana. The Ho West district shares borders with the Republic of Togo, and its capital, Dzolo-Kpuita, is located 175 km northeast of Accra. The total population is 95,000 (20). Anaemia and undernutrition remain critical public health issues in this region. Recent national trends indicate that anaemia prevalence among children under 5 years, although decreasing, remains alarmingly high at 48.9% as of 2022, down from 76.1% in 2003 (21). In the Volta Region specifically, hospital-based data shows that over 55% of children under five are anaemic (22). Stunting, a marker of chronic undernutrition, also affects nearly one in five children under five in Ghana (23). In the Ho West district, 73.5% of the people work in agriculture in some capacity. Less than 1 % (0.06%) of households involved in agriculture are involved in fish farming, with the majority (95.2%) in crop farming (47). Farmers in this region cultivate a diverse range of fruits and vegetables, including bananas, pineapples, mangoes, pears, and oranges. These four farming communities, Abutia Kissiflui, Dededo, Amedzofe, and Kpedze, will be the focus of the study. The district’s busiest market, located in Abutia Kissiflui, generates up to 75% of the district’s tax revenue. Contributions from Dededo, Amedzofe, and Kpedze are 12.3, 8.7, and 4%, respectively. Kpedze has a population of 4,692 people, of which 12% are children under the age of five and 51% are women. There are 3,360 people living in Dededo, 16% of whom are children under five, and 53.3% of whom are women. A total of 1,561 people reside in Amedzofe, with 51.2% of them being women and children. With 1,667 residents, Abutia Kissiflui has a female population of 54% and a child population of 13.5% (20, 24). The district’s southernmost neighbourhoods, Kpedze and Amedzofe, were selected for the intervention group, while the northernmost neighbourhoods, Dededo and Abutia Kissiflui, were designated as the control group. Out of the 14 towns in the district, these towns were specifically chosen. To prevent contamination, the control and intervention groups were selected based on their proximity to one another and their geographic location. Also, data on nutritional treatments and services provided in each group will be recorded.

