### Randomisation and allocation procedure

Cluster randomisation will be employed to ensure baseline comparability between the intervention and control groups for key characteristics, including age, weight, and known risk factors. The four selected farming communities will be stratified by geographic location (north and south of the district). Within each stratum, one community will be randomly allocated to the intervention group and one to the control group. Randomisation will be performed by an independent researcher using a computer-generated random number sequence. Allocation will be concealed from the field research team to reduce the risk of selection bias. Due to the nature of the intervention, blinding participants will not be feasible, as the differences between intervention and control conditions are easily observable. However, to minimise bias, the researcher responsible for delivering the intervention will be different from the researcher responsible for allocating clusters. Additionally, outcome data will be collected by individuals blinded to group assignment (44).

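### Whole communities are allocated, two per arm, but arms are compared with individual-level t-tests and chi-square tests; if outcomes are correlated within community, the p-values are too small

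*Protocol article*

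**What the plan says.** The section Randomisation and allocation procedure makes the community the unit of allocation: "Cluster randomisation will be employed to ensure baseline comparability between the intervention and control groups". It stratifies four communities by north and south and adds: "Within each stratum, one community will be randomly allocated to the intervention group and one to the control group".

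The section Intervention design and strategy confirms that treatment follows the community. It targets "women and children in the intervention communities of Kpedze and Amedzofe", with Abutia Kissiflui and Dededo unexposed.

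The Statistical analysis section then names the tests. For continuous outcomes: "A t-test will be conducted to compare the mean differences of the outcomes of interest", within and between groups. For categorical data: "A chi-square test will be done to assess the relationship between categorical variables", with Fisher's exact test. Rank-type tests are foreseen for non-normal data, and 0.05 is the threshold throughout. The one regression concerns drivers of loss and adjusts for age and gender. Repeated-measures analysis or Bonferroni correction is offered for time points and multiplicity. Community appears only as an example of an exploratory subgroup.

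On size, the section Sample size calculation says: "A total of 140 households (70 per group) were determined to be sufficient". It mentions no ICC or design effect.

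**The concern.** A two-sample t-test or chi-square test takes its standard error from variation between individuals. When whole communities are allocated, differences between communities that have nothing to do with the intervention (market access, local crops, health services, season) also enter the arm contrast. With two communities per arm they are averaged over only two units a side, and the planned tests ignore them.

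Anaemia status, dietary diversity and anthropometry are primary outcomes in Table 2, and every between-arm result on them would be affected. Ordinary differences between communities could be reported as intervention effects, in a trial whose Summary expects to inform policy.

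**Working it through.** **The plan's own figure.** The 70 households per group cannot be rebuilt from the stated inputs, because the 30% improvement has no baseline proportion or SD. It does match an individually randomised formula with an assumed effect of 0.5 SD: n = 2(1.96 + 0.84)²/0.5² ≈ 63 per arm, and 63/0.9 = 70. That calculation has no allowance for clusters.

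**Inputs.** There are 2 communities and 70 households per arm, with 10% non-response (protocol). Analysed per community: m = 70 × 0.9 / 2 = 31.5. The equal split is an assumption; Study setting gives community populations from 1,561 to 4,692. The ICC range of 0.005 to 0.10 is also an assumption.

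**Error rate of the planned test.** Design effect DE = 1 + (m − 1) × ICC. True error of a nominal two-sided 5% test = 2 × [1 − Φ(1.96/√DE)].

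| ICC | DE | 1.96/√DE | True error | Simulated (t-test) |
|---|---|---|---|---|
| 0.005 | 1.15 | 1.83 | 6.8% | 6.7% |
| 0.01 | 1.31 | 1.72 | 8.6% | 8.7% |
| 0.02 | 1.61 | 1.54 | 12.2% | 12.4% |
| 0.05 | 2.53 | 1.23 | 21.7% | 22.0% |
| 0.10 | 4.05 | 0.97 | 33.0% | 33.9% |

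With all 35 per community analysed, the formula gives 7.0%, 9.0%, 13.1%, 23.3% and 35.0%. A simulated chi-square test with 35 per community, at the 48.9% anaemia prevalence quoted in Study setting, gave 9.3%, 13.3%, 24.2% and 36.2% for ICC 0.01 to 0.10.

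**A test that respects the allocation.** A t-test on the four community means has 2 degrees of freedom and a critical value of 4.30. In simulation it held about 5% at every ICC tried. Its power for an assumed 0.5 SD effect follows from a non-central t with δ = 0.5/√[ICC + (1 − ICC)/35]. For example, at ICC 0.05, δ = 0.5/√0.0771 = 1.80 and power is 19%. Across ICC 0, 0.01, 0.02, 0.05 and 0.10 the power is 38%, 31%, 26%, 19% and 14%. The individual-level calculation with 70 per arm would suggest about 84%.

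**Exact randomisation test.** With free allocation of 2 of 4 communities there are 6 arrangements, so the smallest two-sided p is 2/6 = 0.33. With one community per arm in each of two zones there are 4 arrangements, so it is 2/4 = 0.50. Both figures presuppose that allocation was really random.

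**Mixed model.** In a balanced design with four communities, the community variance is estimated as zero when the between-community mean square (2 df) falls below the within-community one. The probability is P[F(2, 4(m − 1)) < (1 − ICC)/(1 + (m − 1)ICC)]. With m = 31 this is about 53%, 46%, 32% and 20% at ICC 0.01, 0.02, 0.05 and 0.10. In those trials, software that reverts to individual-level degrees of freedom returns the naive test.

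**Arms against zones.** The allocation section promises one intervention and one control community within each zone. Study setting instead says: "Kpedze and Amedzofe, were selected for the intervention group, while the northernmost neighbourhoods, Dededo and Abutia Kissiflui, were designated as the control group", with the intervention pair described as southernmost. Sampling puts Amedzofe and Kpedze together in the north and the other two in the south. The two sections disagree on which zone is which, but both place the intervention communities in one zone and the controls in the other.

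**The case against.** The strongest reply is that the size of the problem is unknown. The document gives no ICC, and at 0.005 the error rate is only about 7%. Baseline-to-post differences may have a smaller ICC than single measurements. This stands: a reader might infer that the false-positive rate is certainly far above 5%, and the documents do not support that unconditionally. Change scores do not, however, remove community-by-time variation, and the planned tests are valid only if the ICC is essentially zero.

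A second reply is that a separate analysis plan may deal with clustering. An omission could be excused that way, but here the article itself names the between-group test.

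Third, the chi-square sentence speaks of relationships between categorical variables, so its use for comparing arms is an inference. It is a reasonable one, since no other test is named for a categorical outcome.

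Two further readings go too far. The remark on intention-to-treat, "This approach ensures an unbiased estimate of the intervention effect", is not evidence here: ignoring clustering distorts standard errors and does not by itself bias the estimate. Nor does the limit on the exact randomisation test mean that no valid test can reach 0.05. The 2-df t-test can, but it leans on a model and has little power.

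**Conclusion.** The concern holds in conditional form. Allocation is by four communities, the stated between-arm tests are individual-level, and nothing in the Statistical analysis section repairs this. If outcomes are correlated within community, the nominal 5% test has a true error of about 7% at ICC 0.005, rising to 33% at 0.10. This assumes 31.5 analysed in each community and those ICC values.

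Two limits remain after any correction. Four communities leave too little information for a confirmatory test. And if the arms are split by zone, as Study setting and Sampling describe, a zone difference is inseparable from the intervention effect; a wide interval does not reveal that bias. For the same reasons, randomising four clusters cannot guarantee baseline comparability. The change should be made before analysis, and the protocol says that no results have yet been generated.

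**What to change.** - Replace the between-arm individual-level tests, for outcomes measured at both time points, with a comparison of four community summaries. Use community means of baseline-adjusted values for continuous outcomes, and community proportions or risk residuals for binary ones such as anaemia. Compare two against two with a t-test on 2 df and a 95% confidence interval. Post-harvest handling knowledge and practices is listed in Table 2 at baseline only, so it falls outside this comparison.
- Show all four community values with each result.
- Do not rely on a mixed model alone, since its community variance will often be estimated as zero.
- State the low power (about 14–38% for an assumed 0.5 SD effect) and the floor of the exact randomisation test (0.33 free, 0.50 stratified). Describe between-arm results as preliminary estimates, not a confirmatory test at p < 0.05.
- Remove the claim that randomising four clusters will ensure comparability at baseline.
- Reconcile the allocation section with Study setting, Sampling and Intervention design and strategy. State that if arm equals zone, no analysis can separate the two.

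The cost is revised wording and a few lines of analysis code. The real downside is much wider intervals. Recruitment is already complete, so adding communities is no longer simple.
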